
###### **3.6. Cognitive Processing Therapy**

Participants will receive a total of 12 CPT sessions, 2 psychotherapy sessions related to psilocybin, and one psilocybin dosing session over 7 days. Therapy sessions will be completed by one therapist. On days 1 and 2, CPT sessions 1-4 and the preparatory session will be delivered virtually. These sessions include psychoeducation about PTSD, reviewing the impact the trauma has had on the individual, identifying maladaptive trauma-related beliefs, and beginning cognitive restructuring. The participant will have one preparatory session with a trained therapist to build rapport, assess patient readiness and prepare the participant for the psilocybin session. The preparatory session will be completed on day 2 and will last approximately 45 minutes. On day 3, the psilocybin dosing session (6-8 hours) will be completed in person. During the psilocybin session, the therapist’s goal should be directed toward reducing prolonged symptoms of anxiety or agitation. The therapist should be directive during the session when they feel it is necessary to ensure participant safety, but will avoid active coaching or voicing of interpretations. On the day after the dosing session (day 4), integration session and CPT sessions 5 and 6 will be completed virtually. These sessions include continued cognitive restructuring, with an emphasis on challenging blame-related beliefs. In an integration session which will last 1 hour, participants will discuss their experience during the psilocybin session with the therapist. CPT sessions 7–12 will be completed virtually twice a day until day 7. These sessions focus on PTSD relevant themes (safety, trust, power/control, esteem, and intimacy).

All therapy sessions will be audio and video recorded for research, training, adherence monitoring and quality assurance purposes. The recordings are necessary for developing the experimental treatment and assessing adherence to the Treatment Manual. If the videos are being used for matters outside of research and training, participants will be notified and contacted to request permission for use. Participants will have control over any presentation of this material beyond viewing by researchers or regulatory agencies.

The study will use encrypted, secure technology to transfer and store recordings, but there is always a risk of a security breach. The sponsor-investigator is committed to taking preventative measures to avoid such an event. In the case of a security breach, the participant will be notified and all efforts will be made to minimize the dissemination of recorded content.

###### **3.7. Oura Ring Wearable Device**

At least three weeks before baseline, participants will use a commercially available wearable device (Oura Ring) (<https://ouraring.com>) to collect passive data that is relevant to mental health and well-being such as physiological signals, sleep and activity patterns. This device is a passive wearable device that can be used without obstructing one’s daily life. The Oura Ring device has its own mobile app for data visualization and self-management.

The Oura Ring has been successfully used in previous research studies to provide information on the behavior of body systems (e.g., autonomic nervous system, sleep/circadian rhythm) in real-time through accurate measures of physiological parameters, sleep and activity [(66–68)](https://www.zotero.org/google-docs/?BuYY1P). In the proposed study, we will use Oura Ring (Generation 3) to continuously collect activity levels, sleep staging, heart rate (HR), heart rate variability (HRV), respiratory rate, body temperature variability (delta), respiratory rate, and oxygen saturation (SpO2). The description of the physiological signals to be collected by Oura Ring is provided below as follows:

1. Sleep information: Oura Ring performs sleep analysis and stores a set of measurement parameters that summarize each period. The ring calculates the sleep period specific parameters within four hours from the period end, but sleep analysis is always triggered when you open the application. These parameters include bedtime, total duration, awake, light, rapid eye movement (REM), and deep sleep durations, and also heart rate, breathing, temperature changes during sleep.
2. Activity information: Activity summary contains daily activity summary values and detailed activity levels. Activity levels are expressed in metabolic-equivalent of task minutes (MET mins). Oura tracks activity based on the movement and presents the activity score based on duration of low, medium, and high activity levels. The movement is also used for step count and to estimate calories.
3. Readiness information: Readiness score is interpreted from sleep, activity, resting heart rate, heart rate variability, recovery index and temperature scores. A Readiness Score above 85% indicates that you're well recovered. A score below 70% usually means that an essential Readiness Contributor, such as body temperature or previous night's sleep, falls outside your normal range, or clearly differs from recommended, science-based values.

Further information on the features to be collected by the Oura Ring are summarized in Table 1. Data collection via the Oura Ring will occur from screening and continue throughout the end of study. Data collection via Oura will also be de-identified. To be more specific, each participant will be assigned a dummy email address and password which will be used to login to their account on the Oura app. This will ensure that participants are de-identified on this third-party platform (Oura). The wearable device privacy policy will be made available for all potential users to read. The following steps will outline the data collection process of the Oura Ring device.

1. The account and device will be set up by a research member with a corresponding unidentified ID. The data will be anonymous and only identifiable by research members.
2. The raw data (e.g., accelerometer) and derived metrics will be collected to the local devices and synced to its respective server. The Oura Ring platform has its own secure server where the data will be stored independently from active data.
3. The research team will have access to the Oura Ring Application Programming Interface (API) to extract data from its respective server. The API will securely connect to the respective servers to extract available information. Raw data will be inaccessible to the research team and securely stored on Oura’s respective servers. The resultant metrics (e.g., sleep score) that are derived from the raw data will be available to the research team for analysis and be extracted using the Oura Application Programming Interface (API). The data will be securely extracted and stored on the Unity Health Toronto servers.

After follow-up is complete, the device will be returned to the study coordinator and will be cleaned and sanitized before being given to another participant.

**Table 1**. Description of the Oura Ring wearable device and data collection.

| **Description** | **Data Transfer** | **Data elements** |
| --- | --- | --- |
| The Oura Ring is a smart ring that is worn on the finger and passively collects physiological parameters and information on sleep and activity levels of an individual. It is considered a smart ring that uses advanced sensor technology to allow for precise, personalized health insights about one’s body. The device measures daily activity, oxygen saturation, blood pressure, and skin temperature. Additionally, the device scores an individual’s readiness, sleep, and activity levels. | Participants will download and log on to the Oura Ring app. The Oura Ring is to be connected via Bluetooth to the participant's smartphone. The Oura Ring will collect raw data locally and send it to the mobile app when synced. Once the Oura Ring app has access, the data will be stored onto its respective servers. For data analysis, only authorized research members will have access to the data collected by Oura Ring through its respective application programming interface (API). | Physiological and activity data:   - Heart rate - Heart Rate Variability (HRV) - Respiration rate - Daily Activity levels - Oxygen Saturation (SpO2) - Body temperature variability (delta) - Readiness score - Calories   Sleep data:   - Sleep stages: deep sleep, REM, light sleep, and awake periods - Sleep score - Nap detection |

###### **3.8. Duration of Treatment Period**

The intervention will involve 1 dosing day and 14 additional psychotherapy sessions spanning 1 week. Follow-up sessions will be completed weekly from week 2 until week 13 (1 week until 12 weeks post-treatment).

###### **3.9. Concomitant Medication**

Participants will be asked to remain on stable doses of concomitant medications. No medication changes, unless approved or requested by research staff, are allowed during the study. If any changes to concomitant psychotropic medications are required per the patient’s standard of care, the participant will be withdrawn from the study. All prescription and non-prescription medications (including over-the-counter medications, vitamins, and herbal supplements) taken by the participant within 30 days prior to the screening period will be assessed and documented. Concomitant medications will be assessed and documented from the time the participant signs the ICF to their final study visit. Any changes, additions, or discontinuations of any medications are to be documented at each study visit, or as needed. Please see permissible and prohibited medications in section 4.2 and 4.3.

###### **3.10. Outcomes**

###### **3.10.1. Primary Outcome Measures**

Feasibility & tolerability will be measured by:

1. Recruitment rate (minimum threshold: 2-3 participants/month)
2. Withdrawal rate (maximum threshold: 20%)
3. Data completion rate (minimum threshold: 80%)
4. Adherence rate (minimum threshold: 80%)
5. Percentage of participants with AEs (maximum threshold: 20%)

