###### **2.4. Clinical Adverse Event Profile**

Psilocybin is generally tolerated well. Transient anxiety during psilocybin onset (20-100%), transient confusion or thought disorder (17-75%), mild transient nausea (15-33%), transient headache (33-75%), and transient elevated blood pressure (2-34%) or heart rate (6-8%) are the most common AEs with 20 mg to 30 mg of oral psilocybin [(58,59)](https://www.zotero.org/google-docs/?bXTxrX).

Onset of noticeable psychoactive effects typically occurs within one hour, peaks at about two hours after a dose, and loss occurs typically around six hours after the dose [(60)](https://www.zotero.org/google-docs/?icuc6I). Psilocybin reliably induces profound changes in sensory perception, emotion, thought, and sense of self, characterized by marked alterations in all mental functions, including perception, mood, volition, cognition and self-experience [(61,62)](https://www.zotero.org/google-docs/?aPKYWD). These profound changes are often referred to as mystical-type experiences which are defined as having profound and lasting personal value and spiritual significance toward which participants attributed prolonged beneficial improvements in attitudes, mood and behavior [(63,64)](https://www.zotero.org/google-docs/?Mf8JuE). Mystical-type experiences occurring during psilocybin treatment have often been observed to predict later effects on behavior and emotions [(34,63,64)](https://www.zotero.org/google-docs/?pboda4). However, in a study by Gukasyan et al. (2022) mystical experience after psilocybin dosing sessions only predicted self-reported increases in well-being, but did not predict improvement in depressive symptoms [(65)](https://www.zotero.org/google-docs/?UXvS4F).

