Taken together, the safety of psilocybin should be considered in terms of benefit and risk. Within the context of psilocybin administration in a controlled setting, a participant may report visual or auditory disturbances, feelings of unreality, altered sense of time, and other changes in mood or affect. These effects are expected, and may be a necessary component of therapeutic response [(32)](https://www.zotero.org/google-docs/?o0HPa6). Investigators must follow regulatory guidance under 21 CFR 312.32(a) for AE reporting which addresses untoward medical occurrences associated with the use of a drug in humans, whether or not considered drug related. An AE can be any unfavorable and unintended sign (eg, an abnormal laboratory finding), symptom, or disease temporally associated with the use of a drug, without any judgment about causality. However, because self-reports of intrapsychic events associated with psilocybin usage may be neither unfavorable nor unintended, an investigator may not regard the self-reports as AEs but rather as an essential product attribute for therapeutic response. The reporting of psilocybin associated observations as AEs should be informed by this context.

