###### **3.2. Population**

###### **3.2.1. Number of Participants**

A total of 15 participants are planned to be enrolled in the study.

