###### **4.1.6. Recording of Adverse Events**

AEs will be collected from day 1 of treatment week until the end of the study. At each visit, subjects will be asked if they have had any health problems since the previous visit. All AEs will be recorded appropriately, whether or not considered related to the investigational product. This will include AEs spontaneously reported by the patient and/or observed by the staff as well as AEs reported in response to a direct question e.g. “Have you had any health problems since your last visit?”

For each AE, the following parameters will be described: discovery (i.e., spontaneous or solicited); start; end date or ongoing; action taken with regards to investigational product; outcome if the AE caused the patient to discontinue; a statement if the AE fulfills the criteria for a SAE or not; the investigator’s assessment of the causal relationship between the event and the investigational product; intensity of the AE, i.e., mild (awareness of sign or symptom, but easily tolerated), moderate (discomfort sufficient to cause interference with normal activities), severe (incapacitating, with inability to perform normal activities); and resolution.

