###### **4.1.8. Adverse Events of Special Interest**

An adverse event of special interest (AESI) is an AE (serious or non-serious) of scientific and medical concern specific to the study drug, for which ongoing monitoring and immediate notification by the investigator to the sponsor is required. Such AEs may require further investigation to characterize and understand them.

The following events will be reported as AESI:

- Euphoric mood
- Dissociative disorder
- Hallucination
- Psychotic disorder
- Cognitive disorder
- Disturbance in attention
- Mood altered
- Psychomotor skills impaired
- Inappropriate affect
- Overdose
- Intentional product misuse

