###### **7.2. Sample Size**

Because the anticipated effect size is unknown, a formal sample size calculation cannot be completed. For this trial, it is anticipated that 15 participants will be recruited.

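### The 20% ceiling on participants with any adverse event contradicts the protocol's own adverse-event rates, and section 7.1 gives the ceiling no role

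*Protocol*

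**What the plan says.** **The threshold.** Protocol section 3.10.1 lists five primary measures of feasibility and tolerability. The fifth is "Percentage of participants with AEs (maximum threshold: 20"%). Nothing restricts it to serious, severe or drug-related events.

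**The sample.** Section 3.2.1: "A total of 15 participants are planned to be enrolled in the study". Section 7.2 adds that "a formal sample size calculation cannot be completed", so no planning figure supports the ceiling.

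**Expected rates.** Section 2.4 gives rates for 20–30 mg of oral psilocybin, a range that contains the 25 mg trial dose. Examples are "Transient anxiety during psilocybin onset (20-100"%) and "mild transient nausea (15-33%), transient headache (33-75"%). It also gives confusion or thought disorder 17–75%, raised blood pressure 2–34% and raised heart rate 6–8%. The same section describes the drug as well tolerated in general.

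**What is recorded.** Section 4.1.6: "All AEs will be recorded appropriately, whether or not considered related to the investigational product". Collection runs from day 1 of the treatment week, before the day 3 dose, to the end of the study, and participants are asked about health problems at each visit.

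**Psychoactive effects.** Section 2.4 says of self-reported intrapsychic events that "an investigator may not regard the self-reports as AEs". Section 4.1.8 introduces a list that includes hallucination, euphoric mood and altered mood with "The following events will be reported as AESI".

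**The decision rule.** Section 7.1 tabulates AEs by type. It judges a full trial feasible from the confidence limits for adherence, data completion and withdrawal, alongside a minimum recruitment rate. It does not mention the 20% AE ceiling.

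**The concern.** Tolerability is half of the primary objective in section 2.6.1, and criterion 5 is its only threshold based on AEs. A tolerability limit should separate an acceptable drug from an unacceptable one. This one is set below the rate of a single transient symptom in a drug that the protocol already regards as acceptable.

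The trial would then probably report missing a prespecified primary limit, or redefine the limit after the data are known. In either case criterion 5 would say little about tolerability. Because section 7.1 attaches no consequence to it, a reader could not tell what a miss means for the next trial.

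**Working it through.** The protocol derives no figure for this criterion, so there is nothing to reproduce. The check asks how likely the ceiling is to be met if section 2.4 is right.

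**Step 1, the count allowed.** 0.20 × 15 = 3, so the criterion is met with 0 to 3 participants with an AE.

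**Step 2, the formula.** Let p be the true share of participants with at least one AE. The chance of meeting the ceiling is P(X ≤ 3) = Σ C(15, k) p^k (1 − p)^(15 − k), for k = 0 to 3.

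**Step 3, the range of p.** Section 2.4 gives rates by AE type but not how far the types overlap in the same people. Two assumptions are shown.

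- *Full overlap:* p equals the largest single rate. At the lower ends this is headache, 33%. It also requires that no other participant has any AE, related or not, through week 13.
- *Independence:* p = 1 − Π(1 − rate).
  - Four somatic AEs at their lower ends (nausea 15%, headache 33%, blood pressure 2%, heart rate 6%): 1 − 0.85 × 0.67 × 0.98 × 0.94 = 0.475.
  - All six AEs at their lower ends (adding anxiety 20% and confusion 17%): 1 − 0.80 × 0.83 × 0.85 × 0.67 × 0.98 × 0.94 = 0.652.

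**Step 4, results.** For p = 0.33 the four terms are 0.0025 + 0.0182 + 0.0627 + 0.1338 = 0.217. The other rows use the same formula.

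| Scenario | p | P(at most 3 of 15) |
| --- | --- | --- |
| Lower ends, full overlap, no unrelated AE | 33% | 0.217 |
| Somatic AEs, lower ends, independent | 47.5% | 0.028 |
| Headache alone at mid-range | 54% | 0.008 |
| All six AEs, lower ends, independent | 65.2% | 0.0005 |
| Headache alone at its upper end | 75% | 0.00001 |

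**Step 5, what the ceiling would need.** An 80% chance of meeting it requires p of about 15.7%, less than half the lowest headache figure. A true rate of exactly 20% would meet it 65% of the time.

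**Step 6, the discretion in section 2.4.** The latitude covers intrapsychic self-reports. It does not reach headache, nausea, blood pressure or heart rate. The somatic row leaves out anxiety and confusion altogether, and the chance is still only 0.028.

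**The case against.** **No stated decision uses the ceiling.** A reader might infer that a well-tolerated drug would be declared a failure. The protocol does not support that. Section 7.1 only tabulates AEs, its feasibility rule omits criterion 5, and the tolerability hypothesis in section 2.6.1 is tied to a 10% dropout rate. A full trial could still be judged feasible. This stands, and it limits the consequence to missing the limit in section 3.10.1. It also exposes a second fault: a primary threshold with no stated use.

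**The ceiling is not out of reach.** A reader might infer that it is almost impossible to meet. At the 33% floor the chance is 0.22. The much smaller figures need higher rates within the quoted ranges, or independence between AE types, which the protocol does not give. This stands too: the supportable word is improbable.

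**The result does not turn mainly on investigator discretion.** Since the somatic AEs alone make a miss likely, classification of psychoactive effects is a lesser issue. Sections 2.4 and 4.1.8 can also be read together, because an event of special interest must first be an AE. That is fair. What remains is a tension: an experience that section 2.4 allows to be left out may match a listed special-interest event, with no rule for choosing between them.

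**An analysis plan might narrow the count.** It could, but the unqualified ceiling and the rates that contradict it both stand in the protocol, so the protocol needs the correction.

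**Conclusion.** The concern holds. The any-AE ceiling in section 3.10.1 is inconsistent with section 2.4, and a drug behaving as section 2.4 describes would probably miss it. The chance of meeting it is 0.22 at best, 0.028 on somatic AEs at their lower ends, and 0.0005 on all six AEs at their lower ends.

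The best-case figure rests on headache at its minimum, full overlap of all other AEs and no unrelated event. The two smaller figures rest on independence. All three assume that the rates in section 2.4 carry over to these participants.

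Sections 3.10.1 and 7.1 also disagree on what the threshold decides. The documents do not show that the trial would be declared a failure, or that meeting the ceiling is impossible.

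**What to change.** 1. **Section 3.10.1.** Replace the any-AE measure with the percentage of dosed participants who have at least one serious AE, or at least one severe AE judged possibly or probably related to psilocybin. AEs leading to withdrawal need not be added, since criterion 2 already counts withdrawals.
2. **Sections 4.1.1 and 4.1.6.** Use a single definition of severe. Section 4.1.1 requires a definite hazard to health; section 4.1.6 requires incapacity for normal activities. The new measure would otherwise inherit that ambiguity.
3. **The ceiling.** Have the sponsor set and justify a limit for this subset. Carrying over 20% would accept serious AEs in 3 of 15 participants as tolerable, and nothing in the protocol supports that.
4. **Section 7.1.** State what the criterion decides. If it is to follow the confidence-limit approach used for withdrawal, note that even 0 of 15 gives an exact 95% upper limit of 1 − 0.025^(1/15) = 21.8%.
5. **All AEs.** Tabulate them descriptively, as section 7.1 already plans.
6. **Sections 2.4 and 4.1.8.** Reconcile them so that expected acute psychoactive effects are classified the same way in every participant.

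The cost is one amended outcome definition with the matching text changes. Section 4.1.6 already has seriousness, intensity and causality recorded for each AE, so no new data are needed. The harder part is the ceiling: the protocol gives no rate for this subset, so no replacement value can be calculated from it.

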###### **3.10.2. Secondary Outcome Measures**

The secondary outcomes measures include: Clinician-Administered PTSD Scale for DSM-5 (CAPS-5), PTSD Checklist-5 (PCL-5), Patient Health Questionnaire-9 (PHQ-9), Generalized Anxiety Disorder Scale, 7-item (GAD-7), Dissociative Experiences Scale II (DES-II), Pittsburgh Sleep Quality Index (PSQI), World Health Organization Well-Being Index, 5-item (WHO-5), Quality of relationships inventory (QRI), Inventory of psychosocial functioning (IPF), Posttraumatic Maladaptive Beliefs Scale (PMBS), Brief Experiential Avoidance Questionnaire (BEAQ), 24-items Multidimensional Psychological Flexibility Inventory (MPFI-24), Working Alliance Inventory- Short Form (WAI-SF), Difficulties in Emotion Regulation Scale-Short Form (DERS-SF), Self-Compassion Scale-Short Form (SCS-SF), Psychological Insight Questionnaire (PIQ), Emotional Breakthrough Inventory (EBI), Altered States of Consciousness Rating Scale (ASC), and Acceptance/Avoidance-Promoting Experiences Questionnaire (APEQ) (Figure 2).

The **Clinician-Administered PTSD Scale for DSM-5 (CAPS-5)** is a semi-structured clinical interview used to assess index history of DSM-5-defined traumatic event exposure (American Psychiatric Association, 2013), including the most distressing event, time since exposure, and total number of exposures, as well as frequency and severity of posttraumatic stress symptoms, as evidenced by CAPS-5 total score. The CAPS-5 provides diagnostic status (presence versus absence) of PTSD as well as PTSD symptom severity. The CAPS-5 has shown good psychometric properties, including strong internal consistency, interrater reliability, and test-retest reliability [(69)](https://www.zotero.org/google-docs/?nzbbb3).

The **PTSD Checklist-5 (PCL-5)**, a self-report measure designed to follow DSM-5 criteria for assessing PTSD. The PCL-5 is a 20-item self-report questionnaire in which respondents indicate the presence and severity of PTSD symptoms, derived from the DSM-5 symptoms of PTSD (American Psychiatric Association, 2013). Participants indicate how much distress they have experienced due to symptoms such as “Repeated, disturbing memories, thoughts, or images of a stressful experience from the past,” “Trouble remembering important parts of a stressful experience from the past,” and “Feeling irritable or having angry outbursts” on a five-point Likert-type scale (1 = not at all, 5 = extremely). The total PCL-5 score (a sum of all 20 items) provides an index of overall PTSD symptom severity. The PCL-5 has been found to be psychometrically sound, with strong internal consistency, high test-retest reliability, good convergent and discriminant validity [(70,71)](https://www.zotero.org/google-docs/?vUUrVD).

The **Patient Health Questionnaire-9 (PHQ-9)** is used to assess depressive symptom severity. The PHQ-9 includes 9 items which correspond with the nine diagnostic criteria for DSM-5 major depressive disorder. Scores can indicate either no depression, minimal, mild, moderate, moderately severe, or severe depression. There is strong evidence supporting the validity of the PHQ-9 in both the general population and in medical settings. The PHQ-9 also demonstrates good sensitivity to treatment-associated changes in depressive symptom severity [(72,73)](https://www.zotero.org/google-docs/?16FRtA).

The **Generalized Anxiety Disorder Scale, 7-item (GAD-7)** is useful in primary care and mental health settings as a screening tool and symptom severity measure for the seven most common anxiety disorders. Participants choose one of 4 severity scores associated with problems related to the common anxiety disorders and then indicate the degree to which these problems caused functional and/or social difficulties. Scores are determined by calculating the values for each column. A total score is obtained by the sum of all total column values [(74)](https://www.zotero.org/google-docs/?EtQP45).

The **Dissociative Experiences Scale II (DES-II)** is a 28-item, self-report measure of dissociative experiences. Dissociation is often considered a psychological defense mechanism for victims of traumatizing events, and the scale is of particular use in measuring dissociation among people with PTSD [(75)](https://www.zotero.org/google-docs/?rwaM9V).

The **Pittsburgh Sleep Quality Index (PSQI)** is a self-rated questionnaire which assesses sleep quality and disturbances over a 1-month time interval. It consist of 19 items which are grouped into 7 components, including (1) sleep duration, (2) sleep disturbance, (3) sleep latency, (4) daytime dysfunction due to sleepiness, (5) sleep efficiency, (6) overall sleep quality, and (7) sleep medication use. Each of the sleep components yields a score ranging from 0 to 3, with 3 indicating the greatest dysfunction. The sleep component scores are summed to yield a total score ranging from 0 to 21 with the higher total score (referred to as global score) indicating worse sleep quality. In distinguishing good and poor sleepers, a global PSQI score > 5 yields a sensitivity of 89.6% and a specificity of 86.5% [(76,77)](https://www.zotero.org/google-docs/?Am3at3).

The **World Health Organization Well-Being Index, 5-item (WHO-5)** is a short and generic global rating scale measuring subjective well-being. The WHO-5 items are: (1) ‘I have felt cheerful and in good spirits', (2) ‘I have felt calm and relaxed', (3) ‘I have felt active and vigorous', (4) ‘I woke up feeling fresh and rested' and (5) ‘My daily life has been filled with things that interest me'. The respondent is asked to rate how well each of the 5 statements applies to him or her when considering the last 14 days. Each of the 5 items is scored from 5 (all of the time) to 0 (none of the time). The raw score therefore theoretically ranges from 0 (absence of well-being) to 25 (maximal well-being) [(78)](https://www.zotero.org/google-docs/?b01brn).

The **Quality of relationships inventory (QRI)** is a self-report questionnaire used to determine the quality relationships consisting of 25 items that are evaluated on a 4-point Likert scale ranging from 1 = not true to 4 = almost always true. The 25 items yield three dimensions: Support (7 items, e.g., ‘To what extent could you turn to this person for advice about problems?’), conflict (12 items, e.g., ‘How often do you have to work hard to avoid conflict with this person?’), and depth (6 items, e.g., ‘How significant is this relationship in your life?’). The QRI takes about 5 minutes to administer [(79)](https://www.zotero.org/google-docs/?yKuTDH).

The **Inventory of psychosocial functioning (IPF)** is an 80-item self-report instrument measuring PTSD-related functional impairment in the past 30 days. There are seven functional domains evaluated: romantic relationships, family relationships, work, friendships and socializing, parenting, education, and self-care. The IPF was developed to have high content validity, to not confound PTSD symptoms and related impairment, and to not require respondent attributions regarding the cause of impairment [(80)](https://www.zotero.org/google-docs/?HTmiCY).

The **Posttraumatic Maladaptive Beliefs Scale (PMBS)** is a 15-item scale that was developed to measure maladaptive beliefs about life circumstances that may occur following trauma exposure. The scale comprises three subscales: Threat of Harm, Self-Worth and Judgment, and Reliability and Trustworthiness of Others. Scores on each subscale can be derived by summing items within each subscale. A list of subscale items and reverse-code directions are indicated on the measure. Possible scores range from 15-105, and subscale scores range from 5-35 [(81)](https://www.zotero.org/google-docs/?Ptlf2e).

The **Brief Experiential Avoidance Questionnaire (BEAQ)** is a 15-item self-report measure of experiential avoidance, including items such as “The key to a good life is never feeling any pain” and “I work hard to keep out upset feelings”. Participants rate the extent to which they agree with each item on a 6-point scale from 1 (strongly disagree) to 6 (strongly agree), with one item reverse scored. The BEAQ was developed as a short-form of the original Multidimensional Experiential Avoidance Questionnaire (MEAQ). The BEAQ has been shown to have adequate internal consistency (Cronbach’s alpha = 0.80 to 0.84) and good discriminant validity [(82)](https://www.zotero.org/google-docs/?wswq7t).

The **24-items Multidimensional Psychological Flexibility Inventory (MPFI-24)** is a 24-item self-report scale developed to assess the specific components of psychological flexibility and inflexibility proposed in the Hexaflex model of Acceptance and Commitment Therapy (ACT) [(83)](https://www.zotero.org/google-docs/?fX9mcg).

The **Working Alliance Inventory- Short Form (WAI-SF)** is a patient-rated measure of the alliance between a therapist and client. The measure contains a total score and three subscales: agreement on tasks (e.g., "There is a need to clarify the purpose of the session."), agreement on goals (e.g., "There is a shared perception of the client’s goals in therapy"), and development of bonds (e.g., "There is a sense of discomfort in the relationship") [(84)](https://www.zotero.org/google-docs/?2W4edB).

The **Difficulties in Emotion Regulation Scale-Short Form (DERS-SF)** is an 18-item measure used to identify emotional regulation issues in adults. The measure covers 4 dimensions of emotional regulation: awareness and understanding of emotions; acceptance of emotions; the ability to engage in goal-directed behavior and refrain from impulsive behavior when experiencing negative emotions; and access to emotion regulation strategies perceived as effective. The measure has six subscales: Nonacceptance of emotional responses, difficulty engaging in goal-directed behavior, impulse control difficulties, lack of emotional awareness, limited access to emotion regulation strategies, and lack of emotional clarity [(85)](https://www.zotero.org/google-docs/?54nHp0).

The **Self-Compassion Scale-Short Form (SCS-SF)** is a 12-item self-report measure of self-compassion. The measure can be calculated as a total score of self-compassion or the following subscales: Self-Kindness, Self-Judgment, Common Humanity, Isolation, Mindfulness, and Over-Identification. Items are responded to on a scale from 1 (almost never) to 5 (almost always). The SCS-SF was developed as a short-form of the original Self-Compassion Scale (Neff, 2003). The SCS-SF has been shown to have strong validity, including a strong relationship with subscales from the original SCS (i.e., r > .97), as well as good internal consistency (Cronbach’s alpha > 0.86) [(86)](https://www.zotero.org/google-docs/?zgBQEf).

The **Psychological Insight Questionnaire (PIQ)** is a 23-item self-report measure of acute experiences of insight (e.g. awareness into emotions, behaviors, beliefs, memories, or relationships) after taking a psychedelic. The PIQ yields two subscales: (a) avoidance and maladaptive patterns insights (e.g., "Discovered I could explore uncomfortable or painful feelings I previously avoided") and (b) goals and adaptive patterns insights (e.g., "Awareness of my life purpose, goals, and/or priorities"). Participants rate the intensity with which they experienced these forms of insight during their acute psychedelic experience on a Likert-type scale from 0 (No, not at all) to 5 (Extremely). Higher scores indicate a higher level of acute psychological insight. The PIQ shows good internal consistency, discriminant validity from other measures of acute psychedelic experiences, and strong predictive validity in terms of post-psychedelic improvements in well-being and life satisfaction [(87)](https://www.zotero.org/google-docs/?5LBQJH).

The **Emotional Breakthrough Inventory (EBI)** is a recently validated measure of emotional release/breakthrough experienced during the acute psychedelic state. It is a reliable and validated scale that is positively associated with increases in well-being after a psychedelic experience. The EBI consists of eight statements such as “I felt able to explore challenging emotions and memories” and asks about “emotional release”, “closure”, “emotional breakthrough” and “resolution of conflict”. Participants rated the extent to which they agreed with each statement on a 0–10 scale (with 0 being “No, not more than usually” and 10 being “Yes, entirely or completely”) [(88)](https://www.zotero.org/google-docs/?wVWX99).

The **Altered States of Consciousness Rating Scale (ASC)** measures altered states of consciousness. ASC is used to quantify the qualitative subjective experience of psychedelics [(89)](https://www.zotero.org/google-docs/?wqYQ95).

The **Acceptance/Avoidance-Promoting Experiences Questionnaire (APEQ)** is a psychometric self-report tool for measuring aspects of the acute psychedelic experience that are associated with longer-term changes in psychological flexibility [(90)](https://www.zotero.org/google-docs/?k5yh0b).

